## Study Summary

The onset of mental illness across the lifespan is highest among children and youth, with 70% of cases emerging before age 24 [1]. Despite the benefits of early identification and treatment, at-risk members of this age group have great difficulty accessing and receiving the mental health services they need [2-6]. With more than 90% of youth using the Internet [7-9], web-based electronic health (eHealth) and mobile-based health (mHealth) interventions are promising tools for reaching this age group [10-15], potentially bridging the gap for hard-to-reach populations such as young males or other transition-aged youth who have been reluctant to seek services [16-18]. Within this study we define transition-aged youth as those aged 16-29.

Using a partially blinded, two-arm randomized control study design, this project will test the hypothesis that transition-aged youth who use Thought Spot, a youth-driven open-source online and mHealth intervention, will have greater improvement in self-efficacy and intentions towards help-seeking for mental health concerns compared to a control group. The study will also examine whether participants in the intervention arm show greater improvements in health literacy, including awareness of available services and supports, increased self-efficacy in managing their mental health concerns, and a reduction in mental health stigma, compared to the control arm. Participants in the intervention arm will have access to the Thought Spot platform (online and mobile versions), while the control arm will receive usual care (access to campus health services, Web- and print-based information materials).

Our target population for this study is transition aged youth in post-secondary settings. Throughout this document we refer to them as students, participants, and/or youth. To take part in the study, participants must be transition-aged youth [19] of any gender who are currently enrolled in part-time or full-time studies at one of 3 participating postsecondary institutions in the GTA: University of Toronto, Ryerson University, and George Brown College. At baseline, 236 subjects will be recruited for the intervention arm and 236 subjects for the control arm, which amounts to 472 subjects in total. Participants will be compensated for their time. Data will be collected at baseline, 3 and 6 months from all participants through a battery of online questionnaires to measure primary outcomes (changes in help-seeking intentions), help-seeking behaviours and help-seeking attitudes (secondary outcomes) as well as self-reported changes in self-stigma and self-efficacy, data on demographics and general mental health status. The duration of the study is 6 months.

Participants in the intervention arm will additionally complete a usability survey at the 6-month mark to measure usefulness, satisfaction and ease of use of the Thought Spot application. The purpose of the survey is to explore factors related to app acceptance, feasibility and performance that may affect help-seeking intentions, behaviours and attitudes. Based on the usability survey results, a purposeful sample of 15-20 participants who completed this survey will be invited to participate in a 30-minute qualitative interview to better understand enablers and barriers to using Thought Spot and its impact on help-seeking intentions, help-seeking behaviours and attitudes, health literacy, self-efficacy and empowerment. Both study arms will be receiving and completing the exact same set of 6-month survey questionnaires prior to the usability assessments. Therefore, the extra step of usability testing done subsequently with the intervention arm only, should not influence or confound the results.

This study is an innovative randomized control trial, in its testing of a youth-driven mHealth intervention for its effectiveness. The study will extend and advance our understanding of whether mHealth interventions can help bridge the health literacy gap, facilitate increased self-efficacy and lead to appropriate help-seeking for the target population.

## **Rationale & background information**

Seventy per cent of lifetime cases of mental illness will emerge prior to age 24 [1]. While early detection and interventions can address approximately 70% of childhood cases of mental health problems, only about 36% of those youth in need receive mental health support [2]. Within the current social and medical system the act of help-seeking is a relatively unlikely choice for many transition-aged youth [3,4,20,21]. The barriers associated with help-seeking in young adults vary, and are highest when there is lower access to health services, less support from family and friends, and a lower sense of self-worth [22]. The stigma attached to mental illness, as well as embarrassment and fear of confidentiality breaches, are other major barriers associated with help-seeking among young adults [6,10,23-27].

In addition, mental health literacy, a basic understanding of psychological disorders, where to seek mental health information and treatments, and attitudes toward help seeking, is generally poor among transition-aged youth, with many unable to identify the signs of a mental health problem or when professional help is needed [10,28-30]. The occurrence of mental health concerns during this critical developmental period, together with the lack of treatment and support, can result in an array of complications, often including self-medication with alcohol and other drugs, and an inability to thrive socially, academically and vocationally [31].

The gap is clear: 75% of youth are not receiving the services they need [2]. Current avenues for seeking and accessing services are not efficient or effective. With more than 90% of youth using the Internet [7-9], Web-based electronic health (eHealth) and mobile-based health (mHealth) interventions have been identified as promising tools for reaching this age group [10-15], Websites that are easy to navigate and visually engaging are preferred by many young people [32], while interactive elements, such as coaching and crowd-sourcing, are effective and well-received [33]

In collaboration with Ryerson University, OCAD University, University of Toronto (U of T), Faculty of Medicine, ConnexOntario and Kids Help Phone, the Centre for Addiction and Mental Health (CAMH) team worked with over 65 university and college students to develop Thought Spot, a mobile and online resource designed to help increase access to mental health and wellness services. The resource allows users to interact with a crowd-sourced social sharing and navigation platform to find services in their own specific areas using geo-location technology, providing up-to-date information related to services such as primary care, specialized mental health or addictions services, peer support, sexual health, and crisis information, along with wellness-focused services. The goal is to enhance the direct help-seeking intentions, attitudes and behaviours by increasing knowledge of appropriate services for postsecondary students, minimizing the need for intermediaries. Thought Spot makes access to information easy and interactive by mobilizing students to share their knowledge about services, discover wellness options in their area and build peer networks to find mental health and wellness services and supports ('spots') in their vicinity, read reviews and comments from peers, and add their own 'spots'.

## Study aim and objectives

### Aim

This project will evaluate an mHealth intervention, Thought Spot, designed to enable transition-aged youth in postsecondary settings to identify and overcome barriers to obtaining help for mental health and wellness related issues. Our team will evaluate how Thought Spot enhances participant's help-seeking behaviours for mental health support and services, and thereby increasing their use of appropriate mental health and wellness services. Using a randomized control study design, we will test the hypothesis that transition-aged youth using Thought Spot will have greater improvement in self-efficacy and intentions towards help-seeking for mental health concerns compared to the control group.

### Objectives

Primary objective: To evaluate the impact of Thought Spot on intentions in help-seeking for mental health concerns among transition aged youth (youth aged 16-29) enrolled full-time or part-time at a college or university in the Greater Toronto Area (GTA), compared with a control group (who receive usual care; resource pamphlet).

Secondary objective: To examine whether participants in the intervention arm will show greater improvements in health literacy, including awareness of available services and supports, increased self-efficacy in managing their mental health concerns, and a reduction in mental health stigma, compared to the control arm.

Exploratory: To complete an economic evaluation of the Thought Spot intervention compared to usual care to determine the potential cost-effectiveness and financial implications of sustainable and widespread use of Thought Spot throughout Canadian postsecondary campuses.

### Hypotheses

- (1) Transition-aged youth who receive the intervention will have a greater improvement in intentions and self-efficacy in help-seeking for mental health concerns than those in the control group (usual care; resource pamphlet).
- (2) Participants in the intervention arm will also have greater improvements in health literacy, including awareness of available services and supports, increased self-efficacy in managing their mental health concerns, and a reduction in mental health stigma, compared to the control arm.

## Study Design

### Overview

A two-group partially blinded pre-post randomized controlled study is designed to evaluate the impact of the digital platform, Thought Spot, on transition-aged youths self-efficacy in help-seeking behaviours. To maintain partial blindness, researchers administering surveys will not be aware of the group allocation of participants. A researcher who will not be in contact with participants will conduct the randomization. Measurements will be taken over a 6 month period: baseline, 3 months, and 6 months. 472 participants who are enrolled part-time or full-time at one of 3 participating post-secondary institutions (George Brown College, Ryerson University, University of Toronto) who are interested in maintaining or managing their mental health will be recruited and randomized to the intervention arm or the control arm. Please refer to the study flowchart:

[figure not shown]

GAIN-SS – Global Appraisal of Individual Needs – Short Screener  
 GHSQ – General Help Seeking Questionnaire  
 AHSQ – Actual Help Seeking Questionnaire

ATSPPH-SS – Attitudes towards Seeking Professional Psychological Help – Short Form  
 SSOSH – Self-Stigma of Seeking Help Scale  
 YES-MH – Youth Efficacy/Empowerment Scale – Mental Health

## **Methodology**

This is a partially blind study. The process of inviting students and collecting the data will not be done by the researchers who will have contact with students. Missing values will be minimized by reminders sent to participant at least 3 times and the offer of a reward at the end of the 3rd survey. In the invitation stage we will mention the support of the universities, discuss confidentiality, and explain the importance of the research to foster participation and minimize dropouts. We cannot guarantee that control subjects will not interact with intervention subjects causing some contamination, but given the personal nature of mental health conditions we believe this threat will not be highly prevalent. At the analysis stage we will handle missing values with maximum likelihood estimation, which does not disregard dropouts and is unbiased under MAR (Missing at Random) assumption. Demographic variables (e.g., age, gender, academic year) will be included as covariates which should address differences between groups at baseline and improve estimates, even though these differences are not expected due to the randomization.

### **Control group – usual care and pamphlet**

The control group participants will receive a pamphlet that outlines mental health and wellness services across the GTA. Participants within the control group will also have access to usual care including access to campus health services for mental health and wellness and web- and print- based information materials. Customized pamphlets will be created for each participating postsecondary institution. Using equivalent information and headings throughout, the pamphlet will include the main health and wellness program at the designated institution as well as helplines, walk-in services and crisis resources. Since this study revolves around mental health and wellness, our team felt it necessary to provide an additional resource to control group participants. One of the main issues for transition-aged youth is locating and accessing mental health and wellness services. This pamphlet provides information on their school's health and wellness centre as well as general helplines, walk-in counselling services and crisis supports.

### **Intervention group – usual care and access to Thought Spot platform**

The intervention group participants will have access to the Thought Spot platform. This digital platform was designed and produced in partnership with transition-aged youth who are also post-secondary students. The platform maps out wellness and mental health services across the GTA. Users can also privately construct brief journal entries, and connect experiences to moods and locations. All user entries are displayed on a timeline feature within the application that tracks and presents journal entries and services that the user has added to the platform. Private journal entries are not made available to researchers.

Both groups will receive a small compensation for completion of the study (completing all three surveys) to minimize overall attrition.

#### **Inclusion criteria:**

- 1) Aged 17-29 years, inclusive
- 2) Be enrolled in full-time or part-time studies at one of the participating postsecondary institutions: University of Toronto (St. George and Scarborough), Ryerson University, and George Brown College

- 3) All participants must have functional competency in English
- 4) Participants must have a self-reported interest in maintaining or managing their mental health
- 5) Participants must have access to digital devices compatible with the Thought Spot digital platform.

Inclusion criteria will depend entirely on self-reported information from participants. Research staff will not verify through student records, personal identification, or language tests if participants meet the outlined inclusion criteria.

**Exclusion criteria:**

1. Individuals who do not have access to a functional mobile device or computer.
2. Individuals who are actively suicidal.

Exclusive criteria will also depend on self-reported information. Once participants consent to the study, they will fill in the Global Appraisal of Individual Needs-Short Screener. This scale collects information on internalizing or externalizing psychiatric disorders, substance use, suicidality, and crime or violence problems. If participants are actively suicidal, they will be immediately referred to crisis support services.

**Setting**

This RCT will be conducted collaboratively across several partners, and a multi-disciplinary team of experienced health professionals, administrators, researchers and economists, to ensure the successful evaluation of Thought Spot. For the purposes of this project, the primary community will be college and university campuses within the Greater Toronto Area (GTA), including the U of T, Ryerson University and George Brown College.

**Sample size**

To determine the sample size required to test the primary hypothesis that the Thought Spot intervention will cause a greater change in help seeking intentions compared to usual care, as measured by the difference in formal help seeking intentions from 6 months to baseline, a series of Monte Carlo simulations were carried out (with 10000 replications under each test scenario) using SAS System for Windows v.9.4 (SAS Institute Inc. Cary, NC). These simulations assume that the primary hypothesis will be tested using Mixed Effect Models to account for the longitudinal design and contrasts using time and arm to compare the changes from baseline in both arms. We assume that the test will be two tailed and with critical alpha level of 0.05. In order to simulate the data, means and standard deviation, as well as within subject association are assumed to follow published data that used similar study design. A small effect size, equivalent to a Cohen's d of 0.25, was considered (i.e., an average change in the Help-Seeking Scale of 0.41 - which is a change of 15%), within subject correlation of 0.6, attrition rate of 40% and power of 80%. Based on these simulations and specifications, a sample of 236 subjects per arm before attrition should be used.

To prevent dropping below the 60% response rate required, we will examine our response rates for the final T2 surveys (6 month survey) when the first block of approximately 50-100 participants completes the T2 survey at the 6-month mark of the study. We are proposing to recruit an additional 50 participants if we drop below a 65% response rate at that point. The rationale for this decision is to maintain the power for the analysis in this study.

The participants in the intervention arm will be invited to a usability survey at the 6-month mark which measures usefulness, satisfaction and ease of use of the Thought Spot application. The sample for this survey is limited to the intervention arm because only these participants had access to the Thought Spot application.

A purposeful sample of 15-20 participants who completed the usability survey will be invited to participate in a 30 minute in-person or telephone qualitative interview to better understand enablers and barriers to using Thought Spot and its impact on help-seeking intentions, health literacy, self-efficacy and empowerment. The purposeful sampling criteria follows:

- 1) 5-10 participants with lower than average usability study scores and those describing more barriers to use in the open-ended survey questions and/or low-frequency users as indicated by usage reports.
- 2) 5-10 participants with higher than average usability study scores and those describing more ease with use in the open-ended survey questions and/or, “super-users” as indicated by usage reports.

Given that this is a qualitative study, our aim will be data saturation, that is, the point at which no new information or themes are observed in the data. Typically, saturation can be achieved within 15 semi-structured interviews. Therefore, we propose an initial sample of 10-20 students for the qualitative interviews. If we do not reach saturation once we have reached our participant targets, we will continue to recruit new participants until saturation is achieved.

## **Recruitment**

To recruit 472 participants for the RCT, we will use a number of strategies. The recruitment plan was developed through input from: 1) a Thought Spot student research advisory group (group of 30 students from the thought spot student group); 2) focus groups regarding recruitment for the RCT and 3) individual interviews with campus staff and student leaders. This input was gathered through an earlier stage in the project in which youth were engaged to help co-design the Thought Spot app and the research strategy. An academic literature review was also conducted to identify effective research recruitment strategies for transition-aged youth.

This study will use the following tools: 1) recruitment through invitations/letters circulated through a range campus listservs (e.g.: academic department, health promotion, clubs, student life and course-based listservs); 2) posting of recruitment posters (e.g.: on school bulletin boards, at student centres, student residences, libraries, athletic centres, student common areas, CAMH bulletin boards, LCD screens that have powerpoint slide show played on a loop); 3) placing “app cards” where students pick up print-based information (e.g.: waiting rooms at health and wellness or counselling clinics, student centres, clubs and other common areas); 4) posting the study invitation or advertisement on campus websites (e.g.: health and wellness websites, health promotion websites, student club websites; 5) posting the study invitation or advertisement in student newspapers, student magazines or student blogs; 6) presentations/tables and disseminating swag at campus events (e.g.: health fairs, anti-stigma events, orientation events, club days, etc.); 7) social media promotion (Twitter, Facebook and Instagram); 8) presentations by research team members to student recruiters (e.g.: residence advisors/dons, student mentors, student club leaders/members); 9) psychology research recruitment sites for students; 10) posting the invitation letter through academic courses that offer course credits in exchange for research participation 11) Word of mouth.

Recruitment for the end-of-study qualitative interviews will occur at the 6-month mark of the study. The last question of the end-of-study usability survey will ask if participants if they would be willing to participate in a 30min in-person or telephone interview about their experiences using Thought Spot (Yes/No) and that additional compensation will be provided. This question will also state that not everyone will be contacted for an interview as spots are limited. Participants will be sampled using a purposeful sampling strategy, described in the Sample Size section, above.

Recruitment supports: The Thought Spot Student Advisory group (TSSG) is a group of transition-aged students who have been participating in the co-creation of the Thought Spot tool throughout the project. They include students in health sciences, design, engineering, health IT. The TSSG will help the research team identify relevant student groups and departments that should be targeted throughout the recruitment process. We will also draw on the expertise of research team members affiliated with the included GTA institutions as well as those institutions' health promotion teams, to help us gain access to relevant student services, groups and departments (e.g., student residences, health disciplines, health informatics, psychology and public health departments).

Consent process: Once participants have responded to the study advertisements, using a study script, a research analyst assigned to this project will explain the study either in-person or by e-mail outlining the study criteria and sending a REDCap link to the consent process. To reduce additional steps during the consent process, participants will be led to a REDCap survey where they will review the inclusion criteria and consent form. Once they've reviewed both components, they will indicate whether they consent to the research study or not. The consent form provides detailed information on the purpose and process of the study, potential risks and confidentiality. If a participant would rather review the consent form in person or by e-mail, they are invited to schedule a meeting with the research analyst.

### **Randomization and blinding**

Through concealed and blocked randomization, the subjects will be randomized to the intervention or control groups. To maintain a partially blinded study, the randomization of participants will be conducted by the research coordinator, who will not conduct data collection or recruitment. Randomization of participants will be set in blocks of 8. Until 4 participants are randomized to one group, the remaining assignments will be to the other group until 8 is complete. This will guarantee a balanced sample size in each study group (intervention and control). Block size will be blinded from researchers conducting recruitment and data collection. This will also eliminate any potential for selection bias and minimize confounding factors. We are using computer-generated random allocation of participants to the intervention and control arms, by means of a randomization module within REDCap. A unique identifier will be assigned to participants after the participant's initial details have been obtained.

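### A fixed block of 8 with a run-out rule leaves 20% to 27% of assignments foreseeable to anyone who knows the block size and the history, so the claim to eliminate selection bias is too strong

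*Protocol*

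**What the plan says.** The Protocol, Randomization and blinding, says: "Through concealed and blocked randomization, the subjects will be randomized to the intervention or control groups". It then fixes a single size: "Randomization of participants will be set in blocks of 8". The rule within a block is: "Until 4 participants are randomized to one group, the remaining assignments will be to the other group until 8 is complete". The sequence is computer-generated in the REDCap randomisation module.

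Roles are separated. The same section states that "the randomization of participants will be conducted by the research coordinator, who will not conduct data collection or recruitment", and the Study Design overview adds: "A researcher who will not be in contact with participants will conduct the randomization". On knowledge of the block size the section says: "Block size will be blinded from researchers conducting recruitment and data collection". The coordinator is not in that list. Nowhere does the Protocol say whether the coordinator can see the block size or the earlier assignments, or in what order consented participants are randomised.

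From this arrangement the section concludes: "This will also eliminate any potential for selection bias and minimize confounding factors".

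**The concern.** In a block of fixed size with equal arms, the rest of the block is determined as soon as one arm is full. Someone who knows the size and has seen the earlier assignments then knows the next arm for certain. Hiding the size from recruiters protects against foreknowledge at recruitment. It does not protect against foreknowledge in the person who carries out the allocation, unless that person is also kept from the size or has no choice about whom to allocate next.

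Consent and baseline questionnaires are completed online before randomisation, so more than one eligible participant could be waiting. If the order of randomisation were open, the person who knew the next arm could decide who receives it. The primary outcome is a self-reported intention score with a small target effect (Cohen's d of 0.25), and an absolute statement about selection bias is likely to be repeated in the trial report. It should therefore be one that the design supports.

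**Working it through.** **Inputs.** Block size 8, four per arm, with the run-out rule (Protocol, Randomization and blinding). Total 472, 236 per arm (Study Summary). The document gives no predictability figure.

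**The plan's own balance.** 472 / 8 = 59 complete blocks, and 59 × 4 = 236 per arm. The stated arm sizes follow from the block design.

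**Forced tail of a block.** Suppose the observer knows the size and all earlier assignments. A tail of length r (1 to 4) is forced when one arm receives its fourth participant at position 8 − r.

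(a) *Run-out rule taken literally* (a fair coin until one arm has four). P(r) = 2 × C(7 − r, 3) / 2^(8 − r):

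- r = 1: 40/128 = 0.3125
- r = 2: 20/64 = 0.3125
- r = 3: 8/32 = 0.25
- r = 4: 2/16 = 0.125

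The expected forced tail is 0.3125 + 0.625 + 0.75 + 0.5 = 2.1875 of 8, or 27.3%. Over 59 blocks that is about 129 of 472.

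(b) *Ordinary permuted block* (all C(8, 4) = 70 orders equally likely). P(r) = 2 × C(7 − r, 3) / 70, which gives 40/70, 20/70, 8/70 and 2/70. The expected forced tail is (40 + 40 + 24 + 8)/70 = 1.6 of 8, or 20.0%. Over 59 blocks that is about 94 of 472.

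Under either reading the last assignment of every block is forced: at least 59 of 472, or 12.5%.

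**Best guess over the whole block.** Always guessing the more likely arm is right 63.7% of the time under (a) and 66.6% under (b), against 50% with no information.

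**Effect of mixed sizes.** Take permuted blocks of 6, 8 and 10 in random order, and an observer who knows the possible sizes but not their order. Simulated trials of 472 give about 1.5% to 1.7% certain assignments. Best-guess accuracy stays near 67%.

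Mixing sizes therefore removes most of the certainty but does not lower the overall guessing rate. What removes the use of any foreknowledge is a fixed order of randomisation.

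**The case against.** The strongest reply is that predictability is not selection bias. Foreknowledge does harm only in someone who influences who enters or in what order. The Protocol keeps the randomiser away from recruitment, data collection and participants. It states that allocation is concealed and computer-generated, and it hides the block size from recruiters. Eligibility is self-reported and consent is given through an online survey. All of this stands, and it makes the remaining route narrow: the coordinator would have to know the size, track the assignments, know something about those waiting, and choose among them. The documents neither describe nor exclude this.

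A second reply is that the run-out sentence may be only a lay description of four-and-four balance, with REDCap using an ordinary permuted list. That is plausible, and it is why 20% is given beside 27%.

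A third is that mixed blocks hardly change the best-guess rate. That is correct, and it is why the order of randomisation matters more than the mix of sizes.

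A reader might infer that about a quarter of assignments were in fact known in advance to the coordinator, or that the treatment comparison is biased by a calculable amount. The documents support neither. They do not say that the coordinator knew the block size, and they give no figure for steering. The primary contrast is also change from baseline, so a stable baseline difference between arms would be subtracted. Bias would need steering related to later change. Nor does the block size being printed in the available Protocol show that recruiters saw it: this version already carries a log of completed analyses.

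**Conclusion.** The point holds in a limited form. With one fixed block size and no stated restriction on what the coordinator may see, 20% (ordinary permuted blocks) to 27% (literal rule) of assignments would be foreseeable to a coordinator who knows the size and the history. That knowledge is an assumption, inferred from the coordinator's absence from the list of those blinded to block size. So is any freedom to choose the order of randomisation, on which the Protocol is silent.

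The safeguards that are stated reduce the risk of selection bias substantially. They do not eliminate it, and the Protocol should not say that they do. No size of bias can be given. This is an inexpensive improvement to the allocation procedure and a correction of an absolute claim, not evidence that the allocation was compromised.

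**What to change.** In Randomization and blinding:

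1. Replace the fixed block and the run-out sentence with an allocation table for the existing REDCap module, made of permuted blocks of randomly mixed sizes (for example 6, 8 and 10). Withhold the sizes and their order from the coordinator as well as from recruiters and data collectors. Certain assignments then fall to about 2%.
2. State that participants are randomised strictly in the time-stamped order in which they complete consent and the baseline questionnaires. This closes the remaining route.
3. Change *eliminate* to *reduce* in the sentence on selection bias.

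The cost is one allocation table and a few lines of text. The one drawback is that the final arm sizes may differ by up to 5 (half of the largest block, if the last block is incomplete), which keeps the stated aim of balance nearly intact.

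The Statistical Analysis Plan Change Log reports analyses as already done, so allocation is probably complete. In that case, correct the claim, say which rule REDCap applied, state whether the coordinator could see the block size and past assignments, and compare the order of randomisation with the consent time stamps. Report any departures from that order.
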